### Data collection

The following data will be collected from medical records: ● **Patient demographics:** Age, sex, BMI, ASA PS ● **Preoperative status:** eGFR, history of diabetes, hypertension, respiratory dysfunction or heart disease, perioperative use of diuretics, insulin, or β2-agonists. ● **Procedural details:** ○ Surgical approach (e.g., thoracoscopic, robot-assisted, or open thoracotomy) ○ Anesthesia method ○ Surgical time, Anesthesia time ○ Duration in the prone position ○ CO₂ insufflation (presence, duration, and pressure) ○ Bronchial blocker usage ● **Hemodynamics and fluid balance:** ○ The minimum mean arterial pressure (MAP) during the main surgical phase (prone phase) ○ Intraoperative urine output, Fluid volume, Blood transfusion status ○ Norepinephrine use and total dose ● **Arterial blood gas data:** ○ Serum potassium, pH, PaCO₂, HCO₃ ⁻ , BE, AG, and lactate will be collected at the following three timepoints: ■ **Timepoint 1 (Baseline):** After induction of anesthesia, before surgical positioning or incision. ■ **Timepoint 2 (Intervention):** During the phase of maximal respiratory challenge (e.g., the point of highest PaCO₂ during prone positioning with capnothorax). In cases where arterial blood gas was measured multiple times during the prone phase, the data from the timepoint with the lowest arterial pH will be used for the primary analysis. ■ **Timepoint 3 (Post-procedure):** Immediately upon arrival in the ICU or at the end of surgery.

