## Introduction

Prone positioning has become an increasingly common approach for thoracoscopic esophageal cancer surgery to facilitate surgical exposure. It has been associated with better surgical outcomes and improved perioperative safety compared to the classical lateral decubitus position [1]; however, it may significantly impact ventilation. Partial lung collapse and intrathoracic insufflation of carbon dioxide (CO₂), commonly used in these procedures, may contribute to significant alterations in respiratory physiology and acid-base balance.

Clinically, elevations in serum potassium levels associated with acute respiratory acidosis are often observed during these surgeries. While acidosis is generally known to affect potassium distribution, respiratory acidosis is typically considered to cause only minimal or no elevation in serum potassium compared to metabolic acidosis [2–3]. However, recent clinical reports challenge this view in the setting of critical illness; for instance, Pathak and Nanda described cases of severe, refractory hyperkalemia in COVID-19 patients where acute respiratory acidosis was identified as a major contributing factor [4]. Nevertheless, the combination of prone positioning, ventilatory compromise, and CO₂ insufflation may alter the expected physiological response.

The primary aim of this study is to quantify the magnitude of serum potassium elevation associated with acute respiratory acidosis during prone-position esophagectomy. Furthermore, we aim to explore the physiological drivers of this phenomenon, including the respective contributions of respiratory and metabolic factors. Ultimately, this research may contribute to enhancing the safety of ventilation strategies and optimizing electrolyte management for these complex procedures.

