### Outcomes

#### Primary outcome.

The mean difference in serum potassium levels between the baseline (supine) and the intraoperative (prone) timepoints.

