### Statistical analysis

The selection of the blood gas sample with the lowest pH during the intervention phase is a pre-specified criterion. This approach is not considered a selection bias but is rather a deliberate strategy to focus the analysis on the study’s primary research question: the physiological response, particularly in potassium homeostasis, to the most severe degree of acute acidosis encountered during the procedure.

All statistical analyses will be performed using R version 4.3.2 (R Foundation for Statistical Computing, Vienna, Austria). A p-value of less than 0.05 will be considered statistically significant.

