Beyond this specific surgical procedure, our findings hold potential implications for the management of critically ill patients in the ICU, particularly those with respiratory failure. Patients with conditions such as Acute Respiratory Distress Syndrome (ARDS) often present with comorbid cardiac or renal dysfunction, making them exceptionally vulnerable to the life-threatening consequences of hyperkalemia. Our findings may suggest that hyperacute respiratory acidosis, in particular, warrants closer monitoring of electrolyte balance than previously appreciated. This perspective may also prompt a re-evaluation of permissive hypercapnia strategies. While permissive hypercapnia is employed to protect the lungs, its potential impact on electrolyte homeostasis is not fully understood.

Our exploratory multivariable analysis, by seeking to identify predictors for the magnitude of potassium increase, may help in identifying surrogate markers to define the safe limits of hypercapnia in critically ill patients.

This study has several methodological strengths. First and foremost, the use of a paired-design, where each patient serves as their own control, is a powerful approach to minimize the influence of inter-patient variability. Second, its two-center nature increases the generalizability of our findings. Furthermore, the collection of detailed, serial arterial blood gas data allows for a granular analysis of the acute physiological changes. Finally, our pre-specified plan to conduct a sensitivity analysis demonstrates a rigorous effort to isolate the effects attributable to respiratory changes, thereby strengthening the specificity of our conclusions.

Several limitations of this study should be acknowledged. First, its retrospective design leads to inherent variability in the timing of blood gas sampling and a lack of standardized protocols. Second, our study includes only patients in whom blood gas analysis was performed, potentially introducing selection bias. However, we believe this may have selectively enriched our sample with patients exhibiting more severe respiratory compromise, which aligns with our primary research question. Finally, distinguishing the precise contributions of respiratory and metabolic components to a mixed acid-base disorder is inherently challenging.

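### The prone gas is chosen by lowest pH although the stated aim is respiratory acidosis, and no planned analysis re-selects it

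*Protocol article*

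**What the plan says.** All references are to the protocol article.

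- **Introduction (aim):** to "quantify the magnitude of serum potassium elevation associated with acute respiratory acidosis during prone-position esophagectomy".
- **Data collection, Timepoint 1:** one gas, taken "After induction of anesthesia, before surgical positioning or incision". No rule selects an extreme value.
- **Data collection, Timepoint 2:** "During the phase of maximal respiratory challenge (e.g., the point of highest PaCO₂ during prone positioning with capnothorax"). If there are several prone gases, "the data from the timepoint with the lowest arterial pH will be used for the primary analysis".
- **Primary outcome:** "The mean difference in serum potassium levels between the baseline (supine) and the intraoperative (prone) timepoints".
- **Statistical analysis:** defends the rule as pre-specified: "This approach is not considered a selection bias but is rather a deliberate strategy". The target given there is the potassium response at the worst acute acidosis reached. The word respiratory does not appear in that statement of the target.
- **Secondary outcomes, Sensitivity Analysis:** one re-analysis drops patients with base excess below -5 mmol/L at Timepoint 2. The other keeps only patients with PaCO2 of at least 50 mmHg at that timepoint.
- **Discussion:** presents the sensitivity analysis as controlling for metabolic acidosis and, among the strengths, as a way to isolate respiratory effects. It also concedes that gas timing was not standardised and that "our study includes only patients in whom blood gas analysis was performed, potentially introducing selection bias". Participants, by contrast, says that all eligible prone cases enter.

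**The concern.** The aim and the description of Timepoint 2 are respiratory; the rule that picks the sample is not. pH reflects bicarbonate as well as CO2, so among several prone gases the lowest-pH gas need not be the one with the greatest respiratory load. The prone value is also taken at an extreme of several gases and compared with a baseline that is not.

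Two readings of the result are at stake. The first is whether the mean potassium change describes respiratory acidosis or acidosis in general. The second is whether it describes a typical prone value or the value at the worst moment. The same index gas supplies the changes in PaCO2 and lactate for the correlation and regression analyses, so the choice carries through to them. The Discussion adds weight by saying that a significant rise would by itself point to a phenomenon that challenges current knowledge.

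**Working it through.** The article gives no figure for this point to reproduce. It does not report the number of prone gases per patient, the within-patient SD of potassium, PaCO2 or bicarbonate, or the within-patient correlation of potassium with pH. What follows is therefore a set of assumption ranges.

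**1. Can the two criteria pick different gases?** By Henderson-Hasselbalch, pH = 6.1 + log10[HCO3 / (0.0307 × PaCO2)], so lowest pH means lowest HCO3/PaCO2. Take two gases from one patient:

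- PaCO2 68, HCO3 25: ratio 25/68 = 0.3676
- PaCO2 60, HCO3 22: ratio 22/60 = 0.3667

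The rule takes the second, although its PaCO2 is 8 mmHg lower.

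**2. How often, and in which direction?** Simulation of 200,000 patients, assuming PaCO2 with mean 60 and within-patient SD 8 mmHg, and independent HCO3 with mean 25 and within-patient SD 0.5 to 3 mmol/L. Differences are lowest-pH choice minus highest-PaCO2 choice, averaged over all patients, across that SD range:

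| Prone gases | Different gas chosen | HCO3 difference (mmol/L) | PaCO2 difference (mmHg) |
|---|---|---|---|
| 2 | 5% to 23% | -0.04 to -1.12 | -0.05 to -1.16 |
| 3 | 7% to 35% | -0.07 to -1.75 | -0.08 to -1.88 |
| 4 | 9% to 42% | -0.08 to -2.17 | -0.10 to -2.39 |

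The two criteria agree in most patients. Where they differ, the pH rule moves toward lower bicarbonate and lower PaCO2.

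**3. Shift in the mean potassium change against a typical prone gas.** Shift = r × s × E(m), where r is the within-patient correlation of potassium with falling pH, s is the within-patient SD of potassium, and E(m) is the expected maximum of m standard normal values (0, about 0.56, 0.85 and 1.16 for m = 1, 2, 3 and 5). With r from 0.3 to 0.7 and s from 0.1 to 0.3 mmol/L:

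- m = 1, or r = 0: 0
- m = 2: 0.02 to 0.12 mmol/L
- m = 3: 0.85 × 0.3 × 0.1 = 0.03 to 0.85 × 0.7 × 0.3 = 0.18 mmol/L
- m = 5: 0.04 to 0.24 mmol/L

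Against the pilot mean of 0.73 mmol/L in Sample size estimation, the range for three gases is about 0.025/0.73 = 3% to 0.178/0.73 = 24%.

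**4. Could a shift of this kind alone be significant?** With 150 patients, the pilot SD of 0.53 and no change at a typical prone gas, a shift of 0.05 mmol/L has noncentrality 0.05/0.53 × √150 = 1.16 and would be declared significant in about 21% of studies. A shift of 0.10 has noncentrality 2.31, giving about 63%. This is a limiting case, since the pilot mean is far from zero.

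**5. Do the planned sensitivity analyses cover it?** Both apply a threshold to the Timepoint 2 gas after it has been chosen by lowest pH. A patient whose highest-PaCO2 gas had base excess above -5 can be dropped because another gas had a lower pH and a worse base excess. A patient who stays in still contributes the lowest-pH gas. Neither analysis asks what the potassium change would be at another prone gas.

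**The case against.** The strongest defence is that the rule is explicit and fixed in advance. Highest PaCO2 is introduced only as an example, and lowest pH is the single operative criterion, so nobody extracting data faces an ambiguity. Selection is on pH, never on potassium. If the target is the response at the worst acidosis, the lowest-pH gas is that target by definition. The article also plans two sensitivity analyses, lists the changes in PaCO2 and lactate as candidate covariates, leaves confounding to the secondary analyses, and admits that respiratory and metabolic components are hard to separate. A highest-PaCO2 gas would itself be an extreme of several samples.

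Most of this stands, and it rules out several stronger readings that a reader might infer:

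- *That Timepoint 2 has two contradictory definitions.* It has one rule and a looser description that does not match it.
- *That the primary estimate is inflated.* This holds only against a typical-prone or highest-PaCO2 target, and the shift may be zero.
- *That sicker patients had more gases taken.* This is plausible, but the article says only that timing varied.
- *That the lowest-pH rule must be replaced.* Highest PaCO2 exchanges one extreme for another.

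The defence does not answer two things. Pre-specification prevents picking after the fact, but it does not make the chosen gas specific to respiratory acidosis. And no planned analysis tests how far the result depends on which prone gas was taken.

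**Conclusion.** The point holds in a limited form. The selection rule targets acidosis of any cause, while the aim and the description of Timepoint 2 target respiratory acidosis, and the planned sensitivity analyses do not bridge the gap. They support the Discussion's claim to isolate respiratory effects only in part.

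The size cannot be computed from the article. It is zero with one prone gas or no within-patient correlation between potassium and pH, and about 0.03 to 0.18 mmol/L with three gases under the assumptions above. Set beside a pilot mean of 0.73, a shift of that order is unlikely to account for the whole effect, though the article does not say how the pilot's prone gas was chosen. The primary analysis remains valid for a clearly stated target. This is worth correcting before extraction but does not block the study; confidence is moderate, because every magnitude rests on assumed inputs.

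**What to change.** 1. Extract every prone-phase gas, not only the one with the lowest pH, and report the number of gases per patient.
2. Keep lowest pH as the primary rule if preferred, but state the estimand as the potassium change at the worst acidosis of any cause, and align the description of Timepoint 2 with it.
3. Pre-specify re-analyses of the primary outcome, and of the correlation and regression on the potassium change, with Timepoint 2 re-selected as (a) the highest-PaCO2 gas and (b) the first prone gas after CO2 insufflation or the mean of all prone gases. Set (a) tests whether the result is respiratory; set (b) tests whether it depends on taking an extreme. Fix the choice within (b) in advance.
4. Replace the sentence "This approach is not considered a selection bias but is rather a deliberate strategy" with a statement of what the rule does and does not estimate.
5. Limit the reported mean to patients with a prone gas, and reconcile Participants with the limitation in the Discussion.

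The cost is a few more rows per patient and two extra sets of analyses. The alternative estimates may be somewhat smaller than the headline figure. Study status says that extraction had not begun. If only one prone gas per patient is kept and the data are then anonymised, the question may be hard to reopen.

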### Outcomes

#### Primary outcome.

The mean difference in serum potassium levels between the baseline (supine) and the intraoperative (prone) timepoints.

#### Secondary outcomes.

The secondary outcomes are designed to explore the physiological drivers of the potassium elevation and to test the robustness of the primary finding. They are categorized as follows:

**Analyses of Factors Associated with Potassium Increase:**
**Correlation Analysis:** To explore potential physiological drivers, correlations between the change in serum potassium (ΔK⁺) and changes in other variables will be assessed. These variables will include the change in PaCO₂ (ΔPaCO₂) and markers of metabolic stress, such as the change in lactate (ΔLac).**Multivariable Analysis of** Δ**K** ⁺ **:** A multivariable linear regression analysis will be performed to identify factors independently associated with the magnitude of the serum potassium increase (ΔK⁺). Candidate covariates for the multivariable model include the change in PaCO₂ (ΔPaCO₂), change in lactate (ΔLactate), baseline eGFR, fluid balance, norepinephrine dose, and the duration of the prone position. The final selection of independent variables will be determined based on clinical relevance, assessment of multicollinearity (e.g., variance inflation factor), and the sufficiency of outcome events to avoid overfitting.

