### Study status

The study period covers patients treated between January 2022 and December 2024. While the clinical records for this period already exist, data extraction for this specific research purpose, as well as all statistical analyses, have not yet begun.

We plan to commence data collection (extraction) on or after December 1, 2025, with an estimated completion by March 2026. Authors will not have access to information that could identify individual participants during or after data collection, as all data will be fully anonymized prior to analysis. We anticipate that statistical analysis will be completed and results are expected by May 2026. This protocol is being registered and published prior to data access and analysis to ensure transparency and pre-specify the analytical plan, thereby minimizing the risk of outcome reporting bias.

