#### Analyses for secondary outcomes.

**Analyses of Factors Associated with Potassium Increase:** For correlation analysis, Pearson or Spearman correlation will be used. For multivariable analysis of ΔK ⁺ , a linear regression model will be developed.**Sensitivity Analysis:** The primary outcome will be re-analyzed using a paired t-test on the subset of patients excluding those with severe metabolic acidosis.**Exploratory and Clinical Analyses:** For identifying risk factors for clinical hyperkalemia, a multivariable logistic regression model will be used. For subgroup analyses, the primary outcome will be compared between strata (e.g., using an independent t-test or ANOVA). Other exploratory analyses will be descriptive or use appropriate statistical tests as needed.

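### The linear model of potassium change omits centre, does not guarantee that change in PaCO₂ stays in, and selects terms partly by an events criterion that a continuous outcome cannot have

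*Protocol article*

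**What the plan says.** All references are to the protocol article.

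- **Linear model** (Secondary outcomes, Analyses of Factors Associated with Potassium Increase). "A multivariable linear regression analysis will be performed to identify factors independently associated with the magnitude of the serum potassium increase". The list of candidates begins "Candidate covariates for the multivariable model include the change in" PaCO₂, and continues with change in lactate, "baseline eGFR, fluid balance, norepinephrine dose, and the duration of the prone position". That makes six, and neither centre nor baseline potassium is among them.
- **Selection rule** (same section). "The final selection of independent variables will be determined based on clinical relevance, assessment of multicollinearity", with VIF as the example, and "the sufficiency of outcome events to avoid overfitting". There is no cut-off, and no term is marked as always retained.
- **Statistical analysis, Analyses for secondary outcomes.** It says only that "a linear regression model will be developed".
- **Logistic model** (Exploratory and Clinical Analyses). The outcome is potassium above 5.0 mmol/L. No covariates are named.
- **Availability.** Timepoint 1 potassium is on the Data collection list. Centre is not on that list, but the Participants section names the two hospitals, so it should be known at extraction.
- **Practice and purpose.** The Discussion says "its two-center nature increases the generalizability of our findings". Its limitations paragraph concedes varying blood gas timing and the absence of standardised protocols. Study status says that the article is published to "pre-specify the analytical plan, thereby minimizing the risk of outcome reporting bias".

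**The concern.** The primary outcome is a before-after mean without a comparison group, so it cannot by itself separate a respiratory cause from other effects of surgery. The Introduction makes the respective respiratory and metabolic contributions an aim, and the Discussion looks to the secondary analyses to deal with confounding. The adjusted PaCO₂ slope is one of the main analyses bearing on that question.

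Three features weaken it:

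1. **Centre is left out.** Two hospitals may differ in sampling, anaesthesia and fluids in ways that shift potassium by routes other than PaCO₂. If they also differ in mean PaCO₂ change, the slope absorbs part of the difference.
2. **The adjustment set is open.** If a metabolic term such as lactate change were removed for collinearity with PaCO₂ change, its effect would pass to PaCO₂, and that is the distinction under study.
3. **One selection criterion cannot be applied.** A continuous change has no events to count. The criterion suits the logistic model, which has no covariate list.

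The logistic model raises a related point. Only patients with preoperative potassium of 5.0 mmol/L or more are excluded, and the event is a value above 5.0. Without baseline potassium, the model may partly identify patients who started close to the threshold.

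**Working it through.** The plan gives no figure for the regression models, so there is none to reproduce. Its only inputs here are the target of about 150 cases and the SD of 0.53 mmol/L for the potassium change. It gives no centre-level figures, so every centre difference below is an assumption.

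**1. Room for the terms**

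| Linear model | Terms | Patients per term | Residual df |
|---|---|---|---|
| As listed | 6 | 150/6 = 25.0 | 143 |
| Plus centre | 7 | 150/7 = 21.4 | 142 |
| Plus centre and baseline potassium | 8 | 150/8 = 18.75 | 141 |

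Overfitting is no reason to drop any of the six or to leave out centre.

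**2. Possible bias in the PaCO₂ slope when centre is omitted**

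Let g be the centre difference in potassium change not due to PaCO₂, d the centre difference in mean PaCO₂ change, s the within-centre SD of PaCO₂ change, and p the share of patients at one centre. With PaCO₂ change as the only regressor:

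bias = g · d · p(1−p) / [s² + d² · p(1−p)]

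Assume g = 0.2 mmol/L, d = 8 mmHg, p = 0.5 and a true slope of 0.010 mmol/L per mmHg. The numerator is 0.2 × 8 × 0.25 = 0.4, and d² · p(1−p) = 64 × 0.25 = 16.

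| s (mmHg) | Bias | Inflation |
|---|---|---|
| 8 | 0.4/(64+16) = 0.0050 | 50% |
| 10 | 0.4/(100+16) = 0.0034 | 34% |
| 12 | 0.4/(144+16) = 0.0025 | 25% |
| 15 | 0.4/(225+16) = 0.0017 | 17% |

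**3. Which variable removes the bias**

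Simulation of 2,000 datasets: n = 150, equal centres, s = 10, g and d as above, residual SD 0.45, baseline potassium with true SD 0.3 plus noise SD 0.2, unrelated to centre.

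| Adjustment | Mean slope | Residual variance |
|---|---|---|
| None | 0.0135 | 0.251 |
| Baseline potassium only | 0.0135 | 0.239 |
| Centre only | 0.0101 | 0.243 |
| Both | 0.0101 | 0.230 |

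Centre removes the bias. Baseline potassium does not touch it and only reduces residual variance.

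**4. False-positive rate with a true slope of zero**

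n = 150, residual SD 0.53, equal centres, 4,000 runs per setting, nominal level 5%.

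| g (mmol/L) | d (within-centre SDs) | Without centre | With centre |
|---|---|---|---|
| 0.1 | 0.5 | 5.6% | 4.4% |
| 0.1 | 1.0 | 8.7% | 5.7% |
| 0.2 | 0.5 | 8.1% | 4.7% |
| 0.2 | 1.0 | 16.9% | 4.9% |
| 0.3 | 0.5 | 13.3% | 5.2% |
| 0.3 | 1.0 | 31.4% | 4.5% |

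With small centre gaps the error is close to nominal. With large ones it is not.

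**5. Logistic model**

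The event rate is not given. An assumed 5% to 40% of 150 patients is 7.5 to 60 events. Six terms would then have 1.25 to 10 events each, and eight terms 0.9 to 7.5. Here, unlike in the linear model, the number of events does limit the number of terms.

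**The case against.** The case on the other side is substantial, and several parts of it stand.

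- **Centre confounding is not shown.** A reader might infer that the PaCO₂ slope will reflect a difference between hospitals. The documents do not support that, because they contain no centre-level data. The figures above also concern a slope adjusted for nothing else. The planned model may already carry fluid balance, norepinephrine and other terms that absorb some centre differences, and the residual bias in that model has not been estimated. Centre differences in ventilation or insufflation that act on potassium only through PaCO₂ are variation in exposure, not confounding.
- **Baseline potassium is a different matter from centre.** A reader might infer that its omission also biases the slope. The simulation shows no such effect. It is also a component of the change score, so adjusting for it needs its own rationale.
- **The selection is not purely data-driven.** Clinical relevance is the first criterion, and VIF depends on the predictors, not on potassium. Nothing says that lactate will be dropped. Even so, clinical relevance is undefined and the set remains open.
- **The list may be open, and a separate analysis plan may settle it.** The list is introduced as non-exhaustive, the logistic model has no list, and an article condenses. Silence alone would be no finding. But the article does state a selection rule, and one of its criteria cannot be applied to the model it governs.
- **The analyses are secondary.** The regression is secondary and the Discussion calls the multivariable analysis exploratory. The correlations and the base-excess and PaCO₂ sensitivity analyses also bear on the respiratory question.

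**Conclusion.** The point holds in limited form. Applying an events criterion to a linear model of a continuous change is an error on the face of the text. Leaving centre unnamed in a two-hospital study with acknowledged non-standardised practice, and guaranteeing no place for change in PaCO₂, is a weakness that sits badly with the stated aim of pre-specification. What is not pre-specified is the adjusted PaCO₂ estimate; its place as a candidate and in the correlation analysis is.

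The size rests on assumption. With equal centres and gaps of 8 mmHg and 0.2 mmol/L, an otherwise unadjusted slope is inflated by about 17% to 50% as the within-centre SD runs from 15 down to 8 mmHg. Smaller gaps would do little. The estimate of the primary outcome and its paired test are untouched. This is worth correcting before extraction because it costs almost nothing, not because bias has been demonstrated.

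**What to change.** 1. **Linear model.** Pre-specify the six listed covariates plus centre, with change in PaCO₂, change in lactate and centre always retained. Report VIF, but do not use it to remove terms. Delete the events criterion for this model.
2. **Baseline potassium in the linear model.** Optional, for precision, with a stated rationale because it is part of the change score.
3. **Exploratory logistic model.** Enter baseline potassium and centre first, and limit further terms by the observed number of events. The events criterion belongs here.
4. **Primary outcome.** Report the mean change by centre beside the overall result.

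The cost is protocol wording, centre recorded at extraction, and one degree of freedom in the linear model (two if baseline potassium is added). Data extraction had not begun when the article was written.

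### Three candidate covariates in the ΔK⁺ regression (norepinephrine dose, fluid balance, prone duration) run past the blood gas at which the outcome is measured

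*Protocol article*

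**What the plan says.** **Outcome.** The primary outcome is "The mean difference in serum potassium levels between the baseline (supine) and the intraoperative (prone) timepoints". The multivariable section gives ΔK⁺ no other definition, so I read it as the same change, Timepoint 1 to Timepoint 2. Under Data collection, Timepoint 2 is one gas in the prone phase, given as an example as "the point of highest PaCO₂ during prone positioning with capnothorax". Where there are several prone gases, "the data from the timepoint with the lowest arterial pH will be used for the primary analysis". Neither rule places the sample at the end of the prone phase.

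**Covariates.** Besides ΔPaCO₂ and ΔLactate, the candidates are "baseline eGFR, fluid balance, norepinephrine dose, and the duration of the prone position", with no time window. The matching items under Data collection are:
- "Norepinephrine use and total dose"
- "Intraoperative urine output, Fluid volume, Blood transfusion status"
- "Duration in the prone position"

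The same list does give one variable a window: "The minimum mean arterial pressure (MAP) during the main surgical phase (prone phase").

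**Selection.** Final variables are to be chosen on clinical relevance, multicollinearity and avoidance of overfitting. Timing relative to the outcome is not a criterion. The stated aim is to find factors independently associated with the size of the increase.

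**The concern.** A factor offered as a driver of ΔK⁺ should be measured up to the moment ΔK⁺ is measured. Three candidates are not. The part that accrues after Timepoint 2 could do three kinds of harm:

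- It adds variation unrelated to the outcome, which may attenuate the coefficient.
- For norepinephrine and fluids, it may partly be a response to what the gas showed, so an association could run from outcome to covariate.
- Total prone duration may control poorly for time already spent prone when the sample was drawn. If elapsed time raises both potassium and PaCO₂ (an assumption), the ΔPaCO₂ coefficient, which speaks to the study's main physiological question, keeps some of that confounding.

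The Discussion hopes that predictors from this model may help define safe limits of hypercapnia. That use needs predictors that precede the outcome.

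**Working it through.** The protocol gives no figure for this regression beyond a target of about 150 cases, so there is none to reproduce. The check is a comparison of time windows, followed by illustrations on assumed inputs.

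**1. Windows side by side**

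| Quantity | Ends at | Basis |
|---|---|---|
| ΔK⁺ | Timepoint 2, within the prone phase | Data collection; Primary outcome |
| Prone duration | end of the prone phase | item as listed |
| Norepinephrine | end of the case | explicit: total dose |
| Fluid and urine | end of the case | natural reading of intraoperative |
| ΔPaCO₂, ΔLactate, baseline eGFR | Timepoint 2 or earlier | not affected |

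Timepoint 3 is a separate gas at the end of surgery or on ICU arrival, so whole-case totals extend beyond Timepoint 2.

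**2. Prone duration as a proxy for elapsed time**

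Assume prone duration D has mean 200 and SD 45 min. Let elapsed time be t = f·D, with f uniform on (a, b) and independent of D. Then:
- E[f] = (a+b)/2 and Var(f) = (b−a)²/12
- E[D²] = 200² + 45² = 42,025
- Var(t) = E[f²]·E[D²] − (E[f]·200)²
- R² = E[f]²·45² / Var(t)

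| f range | E[f] | E[f²] | Var(t) | R² | Uncontrolled |
|---|---|---|---|---|---|
| 10–100% | 0.55 | 0.3700 | 15,549 − 12,100 = 3,449 | 612.6/3,449 = 0.18 | 82% |
| 50–100% | 0.75 | 0.5833 | 24,515 − 22,500 = 2,015 | 1,139.1/2,015 = 0.57 | 43% |
| 80–100% | 0.90 | 0.8133 | 34,180 − 32,400 = 1,780 | 1,640.3/1,780 = 0.92 | 8% |

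**3. Attenuation**

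This is a simulation of single-covariate regressions with n = 150, true slope 0.0035 mmol/L per minute up to the sample, residual SD 0.5 and duration 200±50 min. All inputs except n are assumed. The expected slope on total duration is 0.0035 × E[f].

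| f range | Slope on total duration | Power, total duration | Power, time to sample |
|---|---|---|---|
| 20–100% | 0.0021 | 67% | 99.7% |
| 30–70% | 0.0017 | 55% | 83% |
| 80–100% | 0.0032 | 96% | 97% |

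**4. Reverse path for norepinephrine or fluids**

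ΔK⁺ is given mean 0.73 and SD 0.53, from the protocol's preliminary data. Assume that the dose before the sample has no effect, that the parts before and after it each have an underlying SD of 0.5 units, and that the later part rises by 0.3 units per mmol/L of ΔK⁺. With n = 150, total dose is significant at 0.05 in 78% of runs, against about 5% for dose up to the sample. This shows that the path can matter, not that it operates here.

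**The case against.** **Condensed article.** Covariate windows and sample clock times are often left to a fuller protocol or extraction form. A reader might infer from the data list that the time of the Timepoint 2 gas will not be recorded. The article cannot establish that, and the point does not rest on it. It rests on what is stated: a total norepinephrine dose, intraoperative volumes and a full prone duration, offered for a model whose outcome ends earlier.

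**Candidates only.** The final model may drop these variables. That is true, but the selection rule would not drop them for timing.

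**Whole-operation totals.** A reader might call all three covariates whole-operation totals. Only norepinephrine is explicitly a total. For fluids this is the natural reading. Prone duration is a prone-phase quantity, though it still runs past the sample.

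**Size.** A reader might take the 82% as the size of the problem. It is the worst of the three scenarios. If respiratory load builds with time, the lowest-pH rule would tend to pick late samples, and duration would then be a fair proxy. ΔPaCO₂ and ΔLactate may also carry part of any elapsed-time effect in the same model.

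**Reverse causation.** A reader might infer that the coefficients are reverse-causal. Nothing in the protocol suggests that potassium alters prone duration. For norepinephrine and fluids the path is plausible but not shown.

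**Acknowledged limitation.** The Discussion concedes variable timing of gas sampling, but does not connect it to these covariates.

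**Conclusion.** The mismatch stands on the protocol's text, given that ΔK⁺ is read as the Timepoint 1 to Timepoint 2 change. As planned, exposure accrued after the outcome would enter a model meant to identify factors independently associated with that outcome. The coefficients for these covariates may be attenuated and, for norepinephrine and fluids, may partly reflect a response.

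The size cannot be fixed from the document. On the assumed durations, about 8% to 82% of elapsed-time variance stays uncontrolled, depending on where Timepoint 2 falls. At the late end, the loss for prone duration is small. Norepinephrine and fluid totals would still include any later part of the case.

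The reach is limited to the secondary linear model, and to the exploratory logistic model if its outcome is taken at Timepoint 2 and it uses these covariates. A reader might infer that the main potassium result is in doubt. It is not: the primary paired t-test and both sensitivity analyses use none of these covariates. This should be corrected, but it does not threaten the primary result.

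**What to change.** At extraction, record the clock times of prone start, CO₂ insufflation start and the Timepoint 1 and Timepoint 2 gases. In the linear model, and in the logistic model if its outcome is taken at Timepoint 2:

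- replace prone duration by minutes from prone or insufflation start to the Timepoint 2 sample;
- replace total norepinephrine by the cumulative dose up to that sample;
- replace intraoperative fluid balance by the balance up to that sample.

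Keep the whole-case totals for description only.

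**Cost.** Modest extra abstraction from the anesthesia record. By the protocol's own account, extraction had not begun. Interval urine or fluid volumes may be missing for some patients. Where they cannot be recovered, report the totals descriptively and not as factors for ΔK⁺.
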